## Abstract

**Introduction:**

Non-alcoholic fatty liver disease (NAFLD) is a common liver disease characterized by an increase in fat in liver cells. The outbreak of NAFLD is estimated to be 32.4% worldwide, with higher rates in Asia and Iran. Nutritional factors such as excessive calorie intake, high fructose intake, copper deficiency, and increased iron intake play an important role in NAFLD. Since there is no specific treatment for NAFLD, intermittent fasting (IF) diet has been suggested as an alternative treatment for obesity and related complications. Previous studies showed the potential positive effects of IF on metabolic health and the reduction of oxidative stress in NAFLD. This randomized controlled trial (RCT) will be aimed to examine the effect of the IF diet in comparison with a low-calorie diet (LCD) on lipid profile, glycemic status, and liver fibrosis in patients with NAFLD.

**Methods and analysis:**

This is a parallel randomized clinical trial conducted on 52 overweight and obese patients with NAFLD. Participants will be randomly assigned to receive either 16:8 IF (fasting from 8 P.M. to 12 P.M. the next day) or a low-calorie (55% carbohydrate- 30% fat, 15% protein) diet for 12 weeks. Anthropometric measurements, liver assessments, and metabolic evaluations will be assessed before and after the intervention. Primary outcomes include liver steatosis and fibrosis, while secondary outcomes include liver function enzymes, insulin resistance, lipid profile, and anthropometric measurements.

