### Sample size calculation

To compare the studied variables between the two groups, considering the error of 5%, the power of 80%, and the effect size of 0.8 (based on Cohen's criterion), the minimum sample size is equal to 26 people in each group and a total of 52 people will be determined.

*t tests—Means*: Difference between two independent means (two groups)

*Analysis:* A priori: Compute required sample size

*Input:* Tail(s) = Two

Effect size d = 0.80

α err prob = 0.05

Power (1-β err prob) = 0.8

Allocation ratio N2/N1 = 1

*Output*

Noncentrality parameter δ = 2.8844410

Critical t = 2.0085591

Df = 50

Sample size group 1 = 26

Sample size group 2 = 26

Total sample size = 52

Actual power = 0.8074866

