### Study design

A diagram of the study design is demonstrated in Fig. 1. A flow chart of the study process is demonstrated in Fig. 2. A total of 52 patients with NAFLD will be screened based on the inclusion criteria. After participant recruitment from online advertisements and social media, 52 participants who meet the eligibility criteria will be enrolled for the trial. We used stratified block randomization with a block size of 2 Patients will be randomly assigned to either an intervention or control group based on BMI (25–30 and 30–35) and gender (male or female). First, we select patients who meet the criteria. Then that variable is used to match the next person with the first person. After all, two patients with similar characteristics are in the same block. Finally, two subjects in the same block are randomly assigned to either the IF diet or the low-calorie diet using random assignment software. All individuals who meet the inclusion criteria and voluntarily participate in the study will receive complete information regarding the purpose of the study, the type of intervention, and the duration of the study. Then, written informed consent will be obtained from individuals. The current clinical trial will be done based on the Helsinki Declaration. All participants will be informed that all services will be free of charge and that they can withdraw from the study at any time. Each person will be given a pre-made meal plan booklet with a set of menus and recipes for breakfast, lunch, dinner, and snacks based on the recommended diet.

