### Assessment of variables

#### Primary and secondary outcome

The primary outcome of this RCT will be determining the level of steatosis and liver fibrosis stage by FibroScan. The major secondary outcome variables will be the measurement of serum liver function enzymes including aspartate aminotransferase (AST), alanine aminotransferase (ALT), and gamma-glutamyl transferase (GGT), and fasting blood insulin (FBI), fasting blood sugar (FBS), homeostatic model assessment for insulin resistance (HOMA-IR), quantitative insulin sensitivity check index (QUICKI), lipid profile including serum total cholesterol (TC), serum triglycerides (TG), low-density lipoprotein cholesterol (LDL_C), high-density lipoprotein cholesterol (HDL_C) and anthropometric indicators including weight, height, and waist circumference (WC).

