### Statistical analysis

Statistical data will be analyzed using SPSS software version 22. The results will be reported as mean ± standard deviation (SD). The normality of variable distributions will be checked using the Kolmogorov–Smirnov test. If a variable does not follow a normal distribution, a logarithmic transformation will be applied. The independent t-test will be used to compare the consumption of food and nutrients between the two groups, and the chi-square test will be used to compare qualitative variables between the two groups. The analyses will be performed based on the intention-to-treat (ITT) approach. Missing values will be treated according to the linear regression method. ANCOVA with adjustment with baseline values will be used to assess the effect of intervention on dependent variables. *p*-value < 0.05 will be considered statistically significant.

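### Two primary outcomes are each tested at an unadjusted 0.05 with no success rule, and the stated power covers one t-test with all 52 participants supplying outcomes

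*Protocol article*

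**What the plan says.** - **Outcomes.** The abstract (Methods and analysis) states "Primary outcomes include liver steatosis and fibrosis". The section Primary and secondary outcome uses the singular but names the same two measures: "The primary outcome of this RCT will be determining the level of steatosis and liver fibrosis stage by FibroScan". Neither place ranks them or says whether success needs one or both.
- **Threshold.** The Statistical analysis section closes with a single criterion for all tests: a p-"value < 0.05 will be considered statistically significant". Treatment effects are to be assessed by ANCOVA adjusted for baseline.
- **Sample size.** The calculation is made "considering the error of 5%, the power of 80%, and the effect size of 0.8". The test is a two-sided comparison of means, "Difference between two independent means (two groups"), with "Allocation ratio N2/N1 = 1". The result is that "the minimum sample size is equal to 26 people in each group and a total of 52 people will be determined", with an actual power of 0.8074866.
- **Enrolment.** Under Study design, "52 participants who meet the eligibility criteria will be enrolled for the trial". That equals the calculated minimum. The same section lets participants withdraw at any time, and the Statistical analysis section plans regression imputation for missing values.

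**The concern.** The plan names two primary outcomes but sets its error rate and its sample size as if there were one. Without a success rule, a significant result on steatosis alone or on fibrosis alone could be reported as a positive primary result at the 5% level, although two chances were taken. The choice between calling the trial positive on either outcome or only on both would also remain open after the data are seen.

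The power figure has a related limit. It describes one test at 0.05 with every enrolled participant contributing an outcome. Once alpha is divided between the two outcomes, or a few participants are lost, the figure no longer describes a t-test in this trial. At stake are the meaning of a positive primary result and the accuracy of the power quoted for it.

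**Working it through.** **Inputs from the protocol article.** d = 0.80, two-sided alpha 0.05, 26 per arm (Sample size calculation); 52 enrolled (Study design); two primary measures (abstract; Primary and secondary outcome); one threshold of 0.05 and ANCOVA on baseline (Statistical analysis).

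**Assumed, because the article does not give them.** Correlation between the two outcomes (0 to 0.9), number of completers, and correlation between baseline and follow-up (0.3 or 0.5).

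**1. Reproducing the plan's own figure.** With n per arm, the noncentrality is d × √(n/2) = 0.8 × √13 = 2.8844, with 2n − 2 = 50 degrees of freedom and critical t = 2.0086. The noncentral t distribution gives power 0.8075. This matches the article, and 26 per arm is the smallest n that reaches 80%.

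**2. Error over two outcomes, each at 0.05.**
- If either counts and the outcomes are independent: 1 − 0.95² = 0.0975. The upper bound for any dependence is 0.05 + 0.05 = 0.10.
- If either counts and the test statistics are correlated (bivariate normal): 9.1% at 0.5, 8.3% at 0.7, 7.0% at 0.9.
- If both must succeed: at most 5%.

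**3. What each success rule does to power (t-test, 26 per arm, d = 0.8).**

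| Rule | Familywise error | Power |
|---|---|---|
| Each outcome taken alone at 0.05 | 5% per outcome | 80.7% per outcome |
| Either, each at 0.05 | about 7-10% | at least one: 87-97%* |
| Both, each at 0.05 | at most 5% | both: 68-78%* |
| Alpha split, each at 0.025 | at most 5% | 71.6% per outcome |

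*Normal approximation, d = 0.8 on both outcomes, correlation 0.9 to 0 for either and 0 to 0.9 for both.

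**4. Loss of participants (t-test, d = 0.8).**

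| Completers per arm | Power at 0.05 | Power at 0.025 |
|---|---|---|
| 26 | 80.7% | 71.6% |
| 25 | 79.1% | 69.6% |
| 23 | 75.6% | 65.3% |
| 21 | 71.6% | 60.6% |

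**5. The planned ANCOVA.** Adjusting for a baseline with correlation r divides the residual SD by 1/√(1 − r²), so the effective effect size is 0.8/√(1 − r²), with one fewer degree of freedom. That is 0.839 at r = 0.3 and 0.924 at r = 0.5.

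| Setting | r = 0.3 | r = 0.5 |
|---|---|---|
| 26 per arm, alpha 0.05 | 84% | 90% |
| 26 per arm, alpha 0.025 | 76% | 84% |
| 21 per arm, alpha 0.05 | 75.5% | 83% |
| 21 per arm, alpha 0.025 | 65% | 74% |

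At alpha 0.025 with 26 per arm, ANCOVA reaches 80% from a baseline correlation of about 0.42.

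**The case against.** A reader might infer that neither the 5% error nor the 80% power holds. The documents do not support that.

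- **Error.** The article nowhere says that a win on either outcome is enough, and the outcome section speaks of one primary outcome. The 5% holds for each outcome alone and for a rule requiring both. This stands, so the 8-10% must be stated as the consequence of one reading. It does not remove the problem: the text also does not require both, so the reading that inflates error remains open.
- **Power.** With 52 completers and each outcome tested at 0.05, the quoted 80.7% is right. One lost participant per arm costs under two percentage points. With all 52 completing, no single unadjusted rule damages both quantities: either raises error and power, both protects error and lowers power.
- **Sizing by t-test.** Planning on a t-test and analysing by ANCOVA is ordinarily conservative and is not an error. At a baseline correlation of 0.5 the ANCOVA stays above 80% after either an alpha split or a fall to 21 completers per arm, though not after both together. This stands. The article gives no correlation, however, so the offset cannot be relied on, and at 0.3 it is not enough in either case.
- **Unseen documents.** Multiplicity and dropout detail often sits in a full protocol or analysis plan, and incomplete data are addressed here through intention-to-treat and imputation. But the article itself fixes the two primaries, the single threshold, the sizing test and the enrolment number; the point concerns how these fit together. Imputing missing values does not restore the information lost with them.

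**Conclusion.** The point holds in a conditional form, as something that should be fixed. Two primary outcomes at an unadjusted 0.05, with no order and no success rule, permit a familywise error of about 8-10% if either counts and their correlation is between 0 and 0.7. The error is 5% only per outcome or if both must succeed.

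The stated power is correct for what it describes: one t-test at 0.05 with 26 outcomes per arm. Under an alpha split or with 21 completers per arm, the t-test figure is about nine percentage points lower (80.7% − 71.6% = 9.1). Whether the trial as analysed falls below 80% depends on the baseline correlation, which the article does not give.

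The power figures assume d = 0.8 on both outcomes and treat both as continuous, whereas the article names fibrosis by stage. Completer numbers and correlations are assumptions and not predictions for this trial.

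**What to change.** **Primary and secondary outcome, and Statistical analysis.** State how error is controlled over steatosis and fibrosis. Either of these does so:
- *Holm.* The smaller p-value is tested at 0.025 and, if it is significant, the other at 0.05.
- *Fixed order.* The first outcome is tested at 0.05, and the second at 0.05 only if the first succeeds.

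If a fixed order is used, the sponsor should choose it in advance to match the trial's aim. Putting steatosis first is not an automatic choice: the aim in the abstract and in Strengths and limitations names liver fibrosis and does not list steatosis.

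**Sample size calculation.** Restate power for the planned ANCOVA at the resulting alpha, with an explicit number of completers and an assumed baseline correlation, preferably over a range such as 0.3 to 0.5.

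**Cost.** Rewording and a recalculated power figure; no extra patients. The downside is a slightly stricter first threshold under Holm, or a second claim that depends on the first under a fixed order, and possibly a less favourable power figure. Rewording adds no dropout margin; it only shows how much loss the 52 can absorb.

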**Discussion:**

Since obesity and insulin resistance are the most important risk factors of NAFLD, and there is no treatment for it, it seems that lifestyle changes such as low caloric diet like IF and exercise can improve lipid metabolism and liver enzymes.

**Trial registration:**

Iranian registry of clinical trials (IRCT20170202032367N5).

## Introduction

Nonalcoholic fatty liver disease (NAFLD) is one of the most common liver diseases [1, 2] with a variety of conditions including simple steatosis, nonalcoholic steatohepatitis (NASH), and fibrosis [3, 4]. NAFLD is characterized by an increase in the amount of fat within liver cells without excessive alcohol consumption [5]. The prevalence of NAFLD was estimated to be 32.4% worldwide [6] and in Asia, the outbreak of NAFLD is reported to be 29.6% [7]. In addition, in the Iranian population, the prevalence is estimated to be around 33.9% [8]. Diet appears to play an important role in improving NAFLD [9]. Dietary factors involved in this disease include excess calorie intake, amount of carbohydrates consumed, types of fats consumed, high fructose intake, copper deficiency, and increased iron intake [10]. Currently, there is no specific treatment for NAFLD, however, a combination of increased physical activity and nutritional modifications are the best alternative treatments for this disease [11, 12]. Adherence to a variety of diets, including low-fat and low-carbohydrate diets, has been less successful in reducing and maintaining weight loss and improving metabolic risk factors in obese individuals, so preventing or controlling associated risk factors can be considered as an alternative treatment [13–15]. Recently, intermittent fasting (IF) diet has been used to limit daily energy intake to treat obesity and its complications, and as an anti-aging method to extend lifespan compared to traditional low-calorie diets (LCDs( [16, 17]. Several studies suggest that compared to LCD, IF may improve metabolic health including significant reductions in insulin resistance, blood pressure, and blood lipids [18]. Some studies have shown that weight gain is associated with increased inflammation and oxidative stress, which may be one of the triggers of NAFLD [19]. On the other hand, one of the positive effects of the IF diet on reducing oxidative stress was the change in body weight and slight upregulation of the sirtuin-3 gene (SIRT3), which is one of the effective therapeutic strategies in fatty liver [20, 21].

Considering the high complications of this disease and the direct and indirect cost of its complications, it seems that low-cost and effective methods such as IF diets can be effective in controlling and preventing the progression of this disease. Therefore, we decided to investigate the effects of an IF diet on lipid profile, blood glucose, and liver fibrosis markers in patients with NAFLD as a novel disease progression prevention and management method that has been studied to a limited extent [22, 23].

### Methods and analysis

The present study is a parallel randomized controlled clinical trial that will be performed at Masoud Clinic in Tehran, Iran on patients with NAFLD. All patients must complete and sign an informed written consent before completing their registration. The research has been approved by the Bioethics Committee of TUMS, Tehran, Iran (No. IR.TUMS.MEDICINE.REC.1400.682). This RCT was registered on the IRCT web page (IRCT20170202032367N5).

### Participants

Participants with NAFLD will be recruited based on the inclusion criteria. NAFLD will be diagnosed according to the Fibro Scan (Metavir-score ≤ F2 and controlled attenuation parameter (Cap) score > 263). To better reflect population diversity and obtain more generalizable results, individuals will be recruited through popular online advertising applications.

### Inclusion criteria

This clinical trial will be performed on both men and women with NAFLD (Metavir-score ≤ F2 and controlled attenuation parameter (Cap) score > 263), BMI between 25 to 35 kg/m^2^, and aged from 20 to 50 years.

### Exclusion criteria

Patients with the following criteria will be excluded from the clinical trial: pregnancy or breastfeeding, consumption of alcohol, smoking or drug use, suffering from other liver diseases, diabetes, taking hepatotoxic (phenytoin, lithium, tamoxifen, antibiotics), antihyperglycemic, weight loss medications, corticosteroids and persons performed night-shift work, and following a special diet in the past three months.

### Sample size calculation

To compare the studied variables between the two groups, considering the error of 5%, the power of 80%, and the effect size of 0.8 (based on Cohen's criterion), the minimum sample size is equal to 26 people in each group and a total of 52 people will be determined.

*t tests—Means*: Difference between two independent means (two groups)

*Analysis:* A priori: Compute required sample size

*Input:* Tail(s) = Two

Effect size d = 0.80

α err prob = 0.05

Power (1-β err prob) = 0.8

Allocation ratio N2/N1 = 1

*Output*

Noncentrality parameter δ = 2.8844410

Critical t = 2.0085591

Df = 50

Sample size group 1 = 26

Sample size group 2 = 26

Total sample size = 52

Actual power = 0.8074866

### Study design

A diagram of the study design is demonstrated in Fig. 1. A flow chart of the study process is demonstrated in Fig. 2. A total of 52 patients with NAFLD will be screened based on the inclusion criteria. After participant recruitment from online advertisements and social media, 52 participants who meet the eligibility criteria will be enrolled for the trial. We used stratified block randomization with a block size of 2 Patients will be randomly assigned to either an intervention or control group based on BMI (25–30 and 30–35) and gender (male or female). First, we select patients who meet the criteria. Then that variable is used to match the next person with the first person. After all, two patients with similar characteristics are in the same block. Finally, two subjects in the same block are randomly assigned to either the IF diet or the low-calorie diet using random assignment software. All individuals who meet the inclusion criteria and voluntarily participate in the study will receive complete information regarding the purpose of the study, the type of intervention, and the duration of the study. Then, written informed consent will be obtained from individuals. The current clinical trial will be done based on the Helsinki Declaration. All participants will be informed that all services will be free of charge and that they can withdraw from the study at any time. Each person will be given a pre-made meal plan booklet with a set of menus and recipes for breakfast, lunch, dinner, and snacks based on the recommended diet.

**Fig. 1 Fig1:**
[figure not shown]
Diagram of the study design

**Fig. 2 Fig2:**
[figure not shown]
Flow chart of enrolment, intervention, and assessments. The ‘X’ refers to the time of allocation, intervention, and assessment of variables. NAFLD, non-alcohol fatty liver disease

### Intervention

Participants will be randomly assigned to either intervention or control group. During the conversation with the patients, each patient will be assigned to either the IF diet or the LCD. Individuals in the intervention group will follow a 16:8 IF diet that will allow them to consume only water and non-energy beverages such as tea, coffee, and sugar-free chewing gum for 16 h and eat food ad libitum for 8 h. The control group will receive LCD with 3 main dishes and 3 snacks with 55% carbohydrate, 30% fat, and 15% protein (300 kcal less than energy requirements) for 12 weeks.

### Compliance

Participants' food intake will be recorded every week to assess how well they are adhering to their diet. Participants will complete a total of 12 food records. Patients will be requested to report their dietary intakes using home measurements to complete their daily recall. Finally, home measurements will be converted to grams using the brochure provided. Participants' total food intake will be examined using the average of all meal recalls during the intervention period. We will calculate energy intake, micronutrients, and macronutrients from dietary recalls using Nutrition IV software (First Databank, San Bruno, CA, USA) modified for Iranian meals. Text messages will be sent to patients to increase diet compliance and remind them to follow the diet.

### Intervention safety

There are no important side effects associated with fasting diets. To assess possible side effects, the participant will be asked to report any changes during the trial with an assessment of their diet via telephone interview.

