#### Assessment of dietary intake

As mentioned above, dietary intake will be assessed using 24-h dietary recall (including one weekend day and two working days) at baseline, weeks four, eight, and twelve of the intervention. Experienced and trained professionals will collect these recalls from the participants, and the mean intake of food items during these four recalls will be calculated in grams per day. The nutrient intake of individuals will be calculated using N4 software (Nutritionist4).

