In conclusion, because dietary modification is most likely a cost-effective method of disease management and treatment, the results of this study can be applied to the management of NAFLD patients.

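### Harms are gathered by one open question tied to an arm-revealing diet call of unclear timing, after a stated premise of no important side effects, so a low or unequal count could not show safety

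*Protocol article*

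**What the plan says.** The Intervention safety section of the protocol article has two sentences. The first is a statement of fact, without a citation: "There are no important side effects associated with fasting diets". The second is the whole of the described method: "To assess possible side effects, the participant will be asked to report any changes during the trial with an assessment of their diet via telephone".

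Two other sections describe contacts about diet. Under Compliance: "Participants' food intake will be recorded every week to assess how well they are adhering to their diet", giving 12 food records. Under Assessment of dietary intake, which opens by referring back to the earlier text, recalls are taken "at baseline, weeks four, eight, and twelve of the intervention". Neither section says that its contacts are the telephone interviews, and the safety section does not say which contacts it means.

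The Intervention section separates the arms by eating pattern. One arm has a 16-hour fast with free eating in the other 8 hours; the other has three main dishes and three snacks at 300 kcal below requirement. Under Study design, participants are told that "they can withdraw from the study at any time". The Discussion concludes that "the results of this study can be applied to the management of NAFLD patients".

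**The concern.** The safety section states the answer before it describes the measurement. What it then describes has three weak features.

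- **The question is open.** Participants are invited to mention changes, with no symptoms named. How much is reported depends on what each person thinks worth mentioning and on how the caller puts the question.
- **It is joined to a diet assessment.** A caller who goes through what was eaten and when will learn the arm. Without fixed wording and order, nothing in the text keeps the questioning alike in the two arms.
- **The occasion is not fixed.** It could be weekly or every four weeks, and the text does not say whether the question continues once someone stops the diet.

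The efficacy result is not at stake. What is at stake is what may be said about tolerability in a trial whose authors expect to inform patient management. If few side effects are recorded, the count will seem to confirm the premise although the method could have produced it. If the arms differ, the difference could come from the asking rather than from the diets.

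**Working it through.** **The plan's own figure.** The only computed quantity in the article is the sample size. With d = 0.80, n = 26 per arm and df = 50, the noncentrality is 0.80 × √(26/2) = 2.8844, the two-sided 5% critical t is 2.0086 and the power is 0.8075. All three agree with the printed values. With 25 per arm the power is 0.7915, so 26 is the minimum. This check serves only to confirm the arm size used below.

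**How often the question is asked.** Read with the Compliance section, up to 12 times in 12 weeks. Read with the dietary intake section, 3 times after baseline (weeks 4, 8 and 12). The ratio is 12/3 = 4. The text does not settle which applies.

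**What a count of zero could show.** If no events are recorded among 26 and capture is perfect, the upper bound p solves (1 − p)^26 = α.

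- One-sided 95%: 1 − 0.05^(1/26) = 0.109, or 10.9%.
- Two-sided 95%: 1 − 0.025^(1/26) = 0.132, or 13.2%.

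These bounds need only n = 26. They do not measure the weakness of the question; a perfect checklist would give the same bounds.

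**How incomplete capture would act.** The documents give neither an event risk nor a capture rate, so both are assumed here and shown over a range. The chance of recording at least one affected participant among 26 is 1 − (1 − p × s)^26, where p is the true risk and s the share captured.

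| True risk p | s = 100% | s = 50% | s = 25% |
|---|---|---|---|
| 5% | 0.736 | 0.482 | 0.279 |
| 10% | 0.935 | 0.736 | 0.482 |
| 20% | 0.997 | 0.935 | 0.736 |

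**How unequal elicitation would act.** Suppose the true risk is 20% in both arms. The expected recorded number per arm is 26 × 0.20 × s:

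- s = 75%: 3.9
- s = 50%: 2.6
- s = 25%: 1.3

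If one arm is captured at 75% and the other at 25%, the expected counts are 3.9 and 1.3, a threefold gap with no true difference. If the capture rates are exchanged, the gap reverses. The direction cannot be known in advance. The table and these counts show a mechanism and are not an estimate for this trial.

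**The case against.** The strongest reply is that a journal article condenses the full protocol. A symptom list, grading, a schedule for safety contacts and a harms table by arm commonly sit in the full protocol, the case report form or the analysis plan, and their absence here is no fault. That stands, and the point does not rest on it. It rests on what the article does state: a conclusion about safety placed before its measurement, and a named question, channel and occasion.

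Several stronger readings are tempting but not supported:

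- **That reporting is unprompted, or that fasting is said to have no side effects.** Participants are asked, and the sentence says no important side effects. The next sentence provides for possible ones.
- **That harms are lost when someone stops the diet.** No section ends contact at that point. Recalls are scheduled by week, not by adherence, and "The analyses will be performed based on the intention-to-treat (ITT) approach". That statement governs analysis and does not itself create safety contacts, so the text is silent: a risk, not a documented loss. Withdrawing from the study is also a different thing from stopping the diet.
- **That callers are told there is nothing to find.** No instruction to interviewers is described.
- **That harms will be under-counted, or that a difference will be biased toward zero.** No figure in the article shows either, and unequal asking could push a difference either way.
- **That a new pregnancy or an excluded drug started during follow-up would go unseen.** This is inferred from silence, and an open question about changes might elicit both.

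It is also fair to say that a caller who assesses diet will almost always learn the arm, and that a checklist does not prevent this. Fixed wording asked before the diet questions does limit how far that knowledge can shape the answers.

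**Conclusion.** The point holds as a weakness in how safety is stated and ascertained, and it should be put right, although no primary or secondary efficacy result depends on it. The premise sentence is not something this trial could establish: even with complete capture, zero events among 26 is compatible with a true risk of up to 10.9% (one-sided) or 13.2% (two-sided). Collection by an open question within an arm-revealing diet call of unclear timing adds a risk of under-ascertainment and of unequal elicitation. A low count could not then be read as evidence of safety, nor an unequal one as a difference between the diets.

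The bounds rest only on 26 participants per arm with complete follow-up. The sizes attached to incomplete or unequal capture rest on assumed risks and capture rates. How much is missed in practice cannot be judged from the article, and a fuller safety procedure may exist elsewhere.

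**What to change.** In the Intervention safety section:

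1. Delete the premise sentence, or qualify it as an expectation with its source.
2. State which of the planned diet calls carry the safety question, and reconcile the weekly and four-weekly descriptions of diet contacts so that the number of occasions is clear.
3. Keep the open question and add a short fixed symptom checklist, worded identically in both arms and asked before any diet question.
4. State that the same questions are put to participants who stop the diet and, if they agree, to those who withdraw.
5. Report the number of participants with each event, and reasons for stopping, by arm with exact 95% confidence intervals. Note that zero in 26 gives a two-sided interval reaching 13.2%.

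Clinical action on any answer is for the investigator to set.

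The cost is one protocol paragraph, a one-page checklist, a few minutes on calls already planned and one descriptive table; participants who stop or withdraw are asked the same short set of questions. The small downside is that naming symptoms will raise the number of minor complaints recorded in both arms.
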